### Secondary outcomes

The secondary outcome measures are:Difference in mean percent time in target (4–10 mmol/L) range at 12 months between the study groups (from data downloaded from the r-CGM device).Difference in mean diabetes-specific distress at 12 months between the study groups as measured by the Problem Areas in Diabetes (PAID) scale [16].Incremental cost per quality-adjusted life year (QALY) for the intervention relative to control for the trial period, as measured by the EuroQol 5 dimension 3 levels (EQ-5D-3 L) [17].Difference in mean HbA1c (%) at 6 months between the intervention and control groups.

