### Intervention

In brief, intervention group participants will be asked to wear the r-CGM device for a period of 2 weeks every 3 months, i.e. at baseline, 3, 6, 9, and 12 months, as well as having an HbA1c test at those times, and to attend a consultation with their GP (clinic assessment visit (CAV)) to discuss the r-CGM reports. This 3-monthly interval is in keeping with clinical practice guidelines [19]. Intervention participants will also attend a 60-min education session with the study registered nurse credentialed diabetes educator (RN-CDE) which will include instruction on how to wear the r-CGM device and how to interpret the glucose reports from the device to better understand their blood glucose and how this relates to their diabetes self-management and treatment options. The r-CGM device being used in the study is the Abbott FreeStyle Libre Pro® Flash Glucose Monitoring System.

Control group participants will wear the r-CGM device at baseline (blinded) and thereafter will be managed according to usual clinical care. The GP and patient will be prompted to undertake 3-monthly diabetes reviews in keeping with clinical practice guidelines about step-wise regular consideration of treatment intensification. Patients randomised to the control group will also attend an education session with a local CDE, funded by the study if required to ensure financial barriers do not exist. Control group participants will have an r-CGM sensing at 12 months, which will be used in collaboration with their GP in their management of diabetes after the final HbA1c blood measurement and all other trial outcomes have been collected.

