### Statistical analysis

#### Sample size

The sample size is based on an individually randomised controlled trial without accounting for stratification by clinic. Clinical significance was considered to be a difference of at least 0.5% (7 mmol/mol) in mean HbA1c between the groups and is based on current guidelines which recommend intensification of therapy when HbA1c levels remain 0.5% (7 mmol/mol) above target [19]. The sample size was calculated using HbA1c in %. Using a significance level of 0.05, power of 0.8, clinically significant difference of 0.5%, and standard deviation of 1.3% for HbA1c [24], the required number of participants in each group is 108, a total of 216. This is equivalent to a difference in the mean HbA1c of 7 mmol/mol between the groups with a standard deviation of 14 mmol/mol [24]. Assuming a 20% attrition rate, the required sample size inflates to 270 (135 in each group). Allowing for 10% clinic attrition and assuming six participants per clinic, we require 50 clinics with six participants per clinic (150 in each group).

Figure 1 shows the minimum number of clinics and participants per clinic required for 20% participant attrition and 10% clinic attrition. The figure shows that it is possible to recruit 300 participants in a variety of ways; for example, 25 clinics with 12 participants per clinic, 30 clinics with 10 participants per clinic, 50 clinics with six participants per clinic, and 75 clinics with four participants per clinic. Four participants per clinic was the minimum recommended to allow for estimation of the correlation in outcome measure between participants in the same group and clinic. From prior knowledge of recruitment patterns from the Stepping Up Study [24] it was decided to recruit 50 clinics with six participants per clinic.

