#### Statistical modelling

##### Primary and secondary outcomes

Whilst our primary outcome is HbA1c at 12 months post-intervention, we will estimate the between-group difference in mean HbA1c at 6 and 12 months with the same linear mixed-effects model using restricted maximum likelihood estimation. As the data are longitudinal, HbA1c measured at baseline, 6 months, and 12 months will be included in the model as the dependent variable and study groups (intervention and control) and time of the pathology result (baseline, 6, and 12 months) will be collected as fixed effects. A two-way interaction term between study group and time will be included in the model to estimate the between-group difference in mean HbA1c at 6 and 12 months, but we will constrain the estimated baseline means to be equal. The model will include random intercepts for clinic (as individuals will be clustered within clinics) and individuals (as patient measures are repeated within individuals). An unstructured variance-covariance structure will be assumed for the random effects variables as correlations between measurements within individuals and correlations between measurements in participants from the same clinic are expected to be unique.

Age, index of relative socio-economic disadvantage (IRSD), and a history of severe hypoglycaemia are known to be at least moderately associated with HbA1c [9, 27]. In a secondary analysis, the outcome measure will be adjusted for these potential confounders. These measures will be included as fixed effects in the model.

An intention-to-treat (ITT) approach will be used where participants will be analysed according to the study group they were assigned, and all participants will be included in the analysis, consistent with mixed model analysis [28]. The estimated mean HbA1c levels at baseline, 6 months, and 12 months will be plotted for each study group with 95% confidence intervals.

The same statistical modelling approach described for HbA1c will be used for the secondary outcomes, percentage time in target and diabetes-specific distress at 12 months. Transformations for skewed outcome measures will be considered.

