#### Complier average causal effect (CACE) analysis

A blinded review of compliance will be conducted by study investigators and the data management team prior to data analysis to determine whether a CACE analysis is required. If appropriate, CACE analysis will be performed on HbA1c at 12 months (primary outcome) to assess the size of the benefit of the intervention in those who comply with the intervention. Unlike a per-protocol analysis (PP), CACE analysis preserves randomisation when estimating the intervention effect [30]. This is achieved by comparing the mean HbA1c of ‘compliers’ in the intervention group (defined in Table 7) with a similar group of control participants who would have complied if they were offered the intervention. The outcome of the analysis is the CACE effect which represents the difference in mean HbA1c between compliers in the intervention group and their counterpart compliers in the control group.

**Table 7 Tab7:** Definition of a complier for the complier average causal effect (CACE) analysis

The following four requirements must be met for a participant to be considered a complier:	
1. Participant attended the educational session at baseline with the study credentialed diabetes educator (CDE)	
2. General practitioner attended a face-to-face group education session or an education session with the study CDE or completed online training	
3. Participant wore a continuous glucose monitoring (CGM) sensor at baseline, 3 months, 6 months, and 9 months	
4. Participant attended clinic assessment visit (CAV) and discussed sensor trace at baseline, 3 months, 6 months, and 9 months	

The method assumes the same proportion of participants in the control group would have complied with the intervention if it was offered to them as those who did comply in the intervention group (A% in Table 8) [30]. Another important assumption is that mean HbA1c at 12 months is the same for non-compliers in both the intervention and control groups (x in Table 8) [30]. It is this assumption that allows the mean HbA1c of the (expected) compliers in the control group to be calculated (using the observed mean HbA1c in the control group). The CACE effect is then calculated as the difference in mean HbA1c between actual compliers in the intervention group and expected compliers control group. This will be reported with 95% confidence intervals.

**Table 8 Tab8:** Complier average causal effect (CACE) analysis

Status	Intervention group		Control group	

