#### Sensitivity analysis

The missing data patterns will be described and the drop-out rates between the two study groups will be compared. A sensitivity analysis will be performed on the primary analysis for HbA1c at 12 months to test the robustness of the missing data assumption using a pattern-mixture model. Under the mixed-effects model, missing data are assumed to be missing at random [28]. Under this assumption, the difference between the mean of the missing data and the mean of the observed data *δ* is assumed to be zero. In a pattern-mixture model, a range of plausible values for *δ* other than 0 will be considered, where positive values of *δ* would indicate that, on average, participants who have missing data have higher (worse) HbA1c than observed participants, and negative values of *δ* assume participants with missing data have lower (better) mean HbA1c than observed participants. Results for plausible values of *δ* will be examined to determine whether study conclusions change for departures from the missing at random assumption in the primary analysis.

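### Time in target at 12 months depends on wearing the sensor, and reasons for not wearing it may differ by arm; the planned model ignores the HbA1c already collected, and the missing-data sensitivity analysis covers HbA1c only

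*SAP article*

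**What the plan says.** Time in target is the first-listed secondary outcome and has one source: "from data downloaded from the r-CGM device" (Secondary outcomes). Under Intervention, the intervention arm is asked to wear the device at baseline, 3, 6, 9 and 12 months. Controls wear it blinded at baseline, and then "Control group participants will have an r-CGM sensing at 12 months".

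The analysis is fixed by reference to the primary outcome: "The same statistical modelling approach described for HbA1c will be used for the secondary outcomes, percentage time in target" (Primary and secondary outcomes). For HbA1c, that is a mixed model on baseline, 6-month and 12-month values. For time in target, Table 4 lists baseline and 12 months only, and its adjusted analysis adds age and IRSD.

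The plan foresees that some intervention participants will miss sensor rounds. Table 7 makes this a condition of compliance: "Participant wore a continuous glucose monitoring (CGM) sensor at baseline, 3 months, 6 months, and 9 months".

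On missing data, the Sensitivity analysis section says that patterns will be described and drop-out compared between arms. The only analysis of departures from missing at random is specified thus: "A sensitivity analysis will be performed on the primary analysis for HbA1c at 12 months".

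**The concern.** HbA1c comes from a venous sample, so it can be obtained whether or not a participant goes on using the sensor. Time in target cannot: without a 12-month sensor there is no value. In the intervention arm that sensor is the fifth round of the treatment itself; in the control arm it is the second sensor of the trial. Participants could therefore miss it at different rates, or for different reasons, in the two arms.

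The mixed model is valid if the missing values are missing at random given what the model contains. Here that is arm, clinic and baseline time in target, plus age and IRSD in the adjusted version. If intervention participants whose control has worsened are the ones who skip the last sensor, the model fills in their values as if they were doing as well as others with the same baseline. The estimate then leans towards r-CGM. HbA1c at 6 and 12 months would carry information on exactly this, and the model does not use it.

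**Working it through.** **The plan's own figure.** The only power calculation concerns HbA1c: "Using a significance level of 0.05, power of 0.8, clinically significant difference of 0.5"% and "standard deviation of 1.3% for HbA1c". With two-sided alpha, n = 2 × (1.960 + 0.842)² × 1.3² / 0.5² = 106.1, or 107 per group by the normal approximation. The t-based version gives 108, in agreement with "the required number of participants in each group is 108, a total of 216". Then 216 / 0.8 = 270 and 270 / 0.9 = 300. All of this reproduces, but none of it concerns time in target, for which the document gives no SD, missing rate or power.

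**Identity.** Let m be the share missing in an arm and d the amount by which the missing participants' mean lies below that of those observed. The observed-data difference then overstates the intervention by

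bias = m_I × d_I − m_C × d_C.

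With m_I = 20% and d_I = 5, 10 or 15 points:
- 10% uninformative control loss (d_C = 0): 1.0, 2.0 or 3.0 points.
- 10% equally informative control loss: 0.5, 1.0 or 1.5 points.
- 20% equally informative control loss: 0.

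The bias thus comes from a difference between arms in share or mechanism, not from loss as such.

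**What baseline adjustment recovers.** Assumed inputs, none from the document: SD 22 points; correlation of baseline with 12-month time in target 0.5; of 12-month time in target with 12-month HbA1c -0.7; of baseline time in target with 12-month HbA1c -0.35. If loss depends on 12-month HbA1c, conditioning on baseline recovers about 0.5 × 0.35 / 0.7 = 0.25 of the gap. Hence bias ≈ 0.75 × (m_I × d_I − m_C × d_C).

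Large-sample simulation with no true effect, 10% control loss unrelated to HbA1c, and regression on baseline alone (false gain in points):

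| Gap d_I | 20% missing | 30% missing | 40% missing |
|---|---|---|---|
| about 4.5 | 0.7 | 1.1 | 1.35 |
| about 9 | 1.3 | 2.0 | 2.6 |
| about 13 | 2.0 | 3.0 | 3.8 |

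Hand check: 0.75 × 0.2 × 4.5 = 0.68 and 0.75 × 0.4 × 13 = 3.9.

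If the 10% control loss is equally selective, the range runs from about 0.4 to about 2.9. Hand check: 0.75 × (0.2 − 0.1) × 4.5 = 0.34 and 0.75 × (0.4 − 0.1) × 13 = 2.9. With equal shares and the same mechanism in both arms, it is about zero.

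**With HbA1c added.** Adding 12-month HbA1c brings the bias to about 0 in every case. A second set of assumptions (SD 25, loss driven by 6-month HbA1c) gives 0.7 to 2.3 points from baseline alone when control loss is unrelated to HbA1c, and about 0 with HbA1c at baseline, 6 and 12 months. Both runs treat HbA1c as observed for everyone.

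**Against sampling error.** Take 150 randomised per arm, 30% intervention loss (105 left) and 10% control loss (135 left). The standard error is 22 × √(1 − 0.5²) × √(1/105 + 1/135) = 19.05 × 0.130 = 2.48 points. A bias of 2.0 points is 0.8 standard errors and lifts a nominal 5% error rate to roughly 13%; 3.0 points lifts it to roughly 23%.

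**The case against.** A reader might infer that the outcome is lost in one arm only, or that stopping the intervention and losing the outcome are nearly the same event. The document supports neither. Controls also need a 12-month sensor, and one who withdraws or declines it loses the value too. Table 7 counts wear at baseline, 3, 6 and 9 months; the 12-month sensor is not part of compliance, so a non-complier can still supply the outcome. The Intervention section asks the whole intervention arm to wear the 12-month sensor, and people unwilling to use r-CGM are excluded from both arms. Sensor fatigue is plausible, but it is conjecture.

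Nor would a difference in loss go unseen. The comparison of drop-out between arms is not restricted to HbA1c and could show it. What it cannot show is the effect on the estimate.

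The size of the bias is assumed throughout, and the larger figures come from making loss selective in one arm and random in the other. With about 120 sensors per arm the 95% half-width is nearly 5 points (1.96 × 19.05 × √(2/120) = 4.8), so most of the biases shown are below one standard error (about 2.5 points). The near-zero bias after the fix depends on HbA1c being observed; participants who leave the trial, for whom the plan allows 20%, may have none at 12 months.

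Finally, a likelihood model under a stated missing-at-random assumption, with departures examined for the primary outcome only, is conventional. The Discussion itself makes the intention-to-treat claim conditional on that assumption. All of this stands, and it limits the point. It does not remove it: a strongly related measurement is already collected and goes unused for an outcome whose measurement depends on the intervention device.

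**Conclusion.** The point holds in a limited form. For time in target the plan uses no post-baseline information to account for missing 12-month values, and it examines departures from missing at random for HbA1c only, although in this outcome the reasons for missing values may well differ between arms. On the assumptions shown, the false gain is about 0.7 to 3.8 points with uninformative control loss, about 0.4 to 2.9 points with equally selective control loss, and about zero if share and mechanism match. These figures illustrate the risk and do not predict it, because the document gives no missing rates, SD or correlations for this outcome. Using HbA1c largely removes the bias where HbA1c is observed, and less so for participants who leave the trial. The matter concerns a secondary outcome and leaves the primary conclusion untouched. It merits a change because the remedy is cheap.

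**What to change.** In the section on primary and secondary outcomes, specify that time in target is analysed on all randomised participants with HbA1c at baseline, 6 and 12 months as auxiliary information, either by multiple imputation by arm or by a joint longitudinal model of time in target and HbA1c.

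In the Sensitivity analysis section, extend the planned delta analysis to 12-month time in target, with separate deltas for each arm. The sign reverses relative to HbA1c: here a negative delta means worse control among those missing. This step matters most for participants who also lack 12-month HbA1c.

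Report 12-month sensor completeness by arm beside the result in Table 4.

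The sensor schedule needs no change. The cost is SAP wording and modest extra analysis on data already being collected; the interval may be wider in the sensitivity analysis.

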##### Economic evaluation

A within trial economic evaluation using participants’ Medicare costs, pharmaceutical benefit schedule (PBS) costs, hospitalisation costs, self-reported costs, diabetic outcomes (proportion with controlled diabetes, HbA1c ≤ 7 mmol/mol) and quality of life data will be performed using a decision analytic framework [29]. The economic model will construct costs and quality of life associated with the health states ‘controlled diabetes’, ‘uncontrolled diabetes’, and ‘death’. It will be constructed in STATA statistical software [25] based on the original trial data and will utilise linear and generalised linear modelling techniques to determine a cost per QALY gained. The analysis will be conducted from a health system and societal perspective. Costs and benefits will be bootstrapped. The distribution of costs and benefits will be simulated using a probabilistic analysis. The results of the economic modelling will be presented as the mean and 95% confidence interval (CI) of the incremental cost per QALY gained at trial conclusion for the r-CGM study group relative to the control group. Simulated cost-effectiveness will be presented for r-CGM relative to the control via a cost-effectiveness plane and a cost-effectiveness acceptability curve. Univariate and probabilistic sensitivity analyses will be performed to assess uncertainty. Estimates of projected implementation costs across Australia will be estimated.

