## Background

The prevalence of type 2 diabetes (T2D) is rapidly increasing and is expected to reach close to 600 million worldwide by 2030 [1]. Close to 1.3 million Australians have been diagnosed with diabetes, with over 85% having T2D [2].

Early management and maintenance of glycaemic (blood glucose) levels through lifestyle modification and pharmacological treatments can reduce the likelihood of diabetes-related complications [3]. Glycated haemoglobin (HbA1c) is an index of average blood glucose level over the preceding 12 weeks and can be measured in mmol/mol or % [4]. HbA1c can be converted from one unit to the other using the relationship mmol/mol = 10.93 × HbA1c (%) – 23.5 [5]. Current guidelines base treatment intensification recommendations on HbA1c levels [6, 7]. The general HbA1c target in Australia is 53 mmol/mol (7%) [8]; however, the Australian Diabetes Society recommends that targets should also take into consideration factors such as age, duration of diabetes, and risk of hypoglycaemia [9]. Clinical care in general practice can help people with T2D achieve HbA1c targets [10] through adopting an evidence-based “treat-to-target” approach (step-wise treatment intensification through changes to lifestyle, medication doses, and/or prescription of additional medications). However, the majority of people with T2D have an HbA1c above their target level and treatment intensification is commonly delayed beyond clinical need [11]. One contributor to this may be that general practitioners (GP) and people with T2D lack an acceptable, feasible, simple, reliable, and effective method for identifying detailed day-to-day blood glucose patterns (glucose profiles) to guide decisions about treatment intensification.

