### Inclusion criteria

Eligible participants will be aged 18–80 years, active patients of the practice (defined as three or more visits to the practice in the last 2 years), have had T2D for at least 1 year with their most recent HbA1c (in the previous 1 month) ≥ 7 mmol/mol (0.5%) above their individualised target (see below) while on at least two non-insulin hypoglycaemic therapy and/or insulin (therapy stable for the last 4 months). Our general glycaemic target is set at 53 mmol/mol (7%) while patients with a history of severe hypoglycaemia (requiring assistance from a third person) or who report impaired awareness of hypoglycaemia (i.e. are unable or have reduced capacity to recognise the early signs and symptoms of hypoglycaemia, which may impede timely self-treatment) will have a target of 64 mmol/mol (8%). In the setting of this pragmatic trial we will allow GPs to indicate a personalised target for a participant if they feel that it should differ from the two pre-specified targets set out above.

Patient exclusion criteria will include: any debilitating medical condition (e.g. unstable cardiovascular disease (CVD), severe mental illness, end-stage cancer), an estimated glomerular filtration rate (eGFR) < 30 ml/min/1.73m^2^, proliferative retinopathy, pregnancy, lactating or planning pregnancy, unable to speak English/give informed consent, unwilling to use r-CGM or follow study protocol, allergy to adhesive tape, diagnosis of T2D within the past 12 months, and any condition that makes monitoring diabetes using HbA1c unreliable (e.g. haemoglobinopathy, iron deficiency anaemia).

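### The economic evaluation defines controlled diabetes as HbA1c ≤ 7 mmol/mol, which is about 2.8%, so the controlled health state would be empty

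*SAP article*

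**What the plan says.** The Economic evaluation section plans a within-trial evaluation in a decision-analytic framework. One of its listed inputs is "diabetic outcomes (proportion with controlled diabetes, HbA1c ≤ 7 mmol/mol". The same section then says: "The economic model will construct costs and quality of life associated with the health states ‘controlled diabetes’, ‘uncontrolled diabetes’, and ‘death". The cut-off is therefore what separates the two living states of the model.

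Elsewhere the article gives HbA1c targets in paired units:

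- Background: "The general HbA1c target in Australia is 53 mmol/mol (7"%).
- Inclusion criteria: "Our general glycaemic target is set at 53 mmol/mol (7"%).
- Inclusion criteria, for participants with a history of severe hypoglycaemia or with impaired awareness of it: "will have a target of 64 mmol/mol (8"%).
- Tables 3 and 6 refer to a general target of 7%.

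The Background also supplies the conversion between units: "mmol/mol = 10.93 × HbA1c (%) – 23.5". No other part of the article gives a different cut-off for controlled diabetes.

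**The concern.** The number 7 belongs to the percentage scale, but the unit printed beside it is mmol/mol. On that scale it describes an HbA1c far below any target in the article and far below the values at which people enter the trial.

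The slip is easy to overlook because 7 mmol/mol appears legitimately elsewhere as a difference. It is the entry margin ("≥ 7 mmol/mol (0.5%) above their individualised target") and also the clinically significant between-group difference in the Sample size section. Table 2 reports HbA1c in both units, so an analyst could apply the cut-off to the mmol/mol variable and get no software error.

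Incremental cost per QALY is a listed secondary outcome. If every living participant is classed as uncontrolled, the model cannot distinguish the arms on glycaemic control, and trial data cannot inform the costs and quality of life of the controlled state. If the cut-off is repaired only once data are in hand, the state definition is no longer pre-specified, although the Discussion says that the analyses are.

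**Working it through.** **Inputs**

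- Cut-off: 7 mmol/mol (Economic evaluation).
- Conversion: mmol/mol = 10.93 × % − 23.5 (Background), with inverse % = (mmol/mol + 23.5)/10.93.
- Targets: 53 mmol/mol = 7% and 64 mmol/mol = 8% (Inclusion criteria).
- Entry margin: at least 7 mmol/mol (0.5%) above target (Inclusion criteria).
- SD of HbA1c: 14 mmol/mol; planned recruitment: 300 (Sample size).

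**Step 1. Does the formula reproduce the article's own pairs?**

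- 10.93 × 7 − 23.5 = 53.01, stated as 53.
- 10.93 × 8 − 23.5 = 63.94, stated as 64.

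Both reproduce.

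**Step 2. What is the economic cut-off on the % scale?**

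- (7 + 23.5)/10.93 = 2.79%.
- Distance below the general target: 53 − 7 = 46 mmol/mol.

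**Step 3. How far is it from entry values?**

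Under the general target, the lowest entry HbA1c depends on which unit of the margin is used:

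- 53 + 7 = 60 mmol/mol, or
- 7.5%, which is 10.93 × 7.5 − 23.5 = 58.5 mmol/mol.

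Even from 58.5, a participant would have to fall by 51.5 mmol/mol to be classed as controlled.

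**Step 4. How many participants could be at or below each cut-off?**

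The article gives no follow-up mean, so a range is assumed, with a normal distribution and SD 14. For the printed cut-off, z = (7 − mean)/14 and the expected count is 300 × Φ(z). For 53 mmol/mol, the share is Φ((53 − mean)/14).

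| Assumed mean (mmol/mol) | z for cut-off 7 | Expected of 300 at or below 7 | Share at or below 53 |
|---|---|---|---|
| 53 | −3.29 | 0.15 | 50% |
| 60 | −3.79 | 0.02 | 31% |
| 65 | −4.14 | 0.005 | 20% |
| 70 | −4.50 | 0.001 | 11% |

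At 7 mmol/mol the controlled state is effectively empty throughout the range. At 53 mmol/mol it is populated throughout.

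**The case against.** The error itself is hard to dispute; the case on the other side concerns its weight and its repair.

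**Reach.** The planned cost-effectiveness results may survive. QALYs come from EQ-5D-3L utilities by area under the curve (Outcome measures). Table 5 builds total costs from resource categories and divides the cost difference by the QALY difference. No row of Table 5 reports health states or the proportion controlled. This stands and limits the harm. It does not remove it, because the Economic evaluation section says that costs and quality of life will be constructed by state, and the article does not explain how the state model and Table 5 connect.

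**Detectability.** With 7% and 53 mmol/mol paired elsewhere, a careful analyst would probably spot the slip, and a tabulation of 0% against 0% would expose it. That is likely, but it means the definition would be mended after data are available.

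**Intended value.** That 53 mmol/mol was meant is an inference. The Inclusion criteria also allow a target of 64 mmol/mol or one indicated by the GP, and the economic section does not say which target defines control. A dropped phrase such as 7 mmol/mol above target cannot be wholly excluded. The general target of 7% remains much the most plausible reading, and the sponsor should confirm it.

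**Reachability.** That no participant would meet the printed cut-off is inferred from the entry criteria and the SD, not stated. The figures support it.

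**Conclusion.** The concern holds. The printed cut-off of 7 mmol/mol equals 2.79%, is 46 mmol/mol below the article's general target, and contradicts the Background and the Inclusion criteria. Taken literally, the proportion controlled is 0% in each arm and the controlled state has no trial data behind it.

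The conversion rests only on the article's own formula. The near-zero counts also assume a normal distribution, an SD of 14 mmol/mol at follow-up and means between 53 and 70 mmol/mol; the conclusion does not change across that range. The effect is limited to the health-state model and the proportion controlled within one secondary outcome. The primary HbA1c analysis is untouched. The definition cannot be used as written and must be corrected before the economic analysis.

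**What to change.** In the Economic evaluation section, replace the cut-off with HbA1c ≤ 53 mmol/mol (7%), which agrees with the general target stated elsewhere in the article. This is a classification rule for the analysis and does not alter any participant's treatment target. The sponsor should confirm that the general target is meant, and not each participant's individualised target, and record this before the economic data are analysed.

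The cost is one figure in the SAP and a dated note of the correction. No new data are needed, and neither the sample size nor the primary analysis changes.
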